### Secondary Endpoints:

Within individual change over 8-week treatment period (on maximum effective and tolerated dose) compared to change over 8-week observational period, and from Day 0 to Week +36 (i.e. treatment phase) in:

1. Incidence of treatment-emergent adverse events and laboratory values over 36-weeks of treatment to known frequency of anakinra-related AEs in other populations.
2. MDRI comprised of:
  - Sanfilippo Behavior Rating Scale (SBRS): Minimal Clinically Important Difference (MCID) = 0.25 SD for each scale
  - Child Sleep Health Questionnaire (CSHQ): MCID = 1-point change 
  - Autism Parenting Stress Index (APSI): MCID = 0.25 SD for Stress Total 
  - PROMIS Fatigue - Parent Proxy Custom Short Form: MCID = 3-point change
  - Movement disorder (e.g. dystonia, chorea, etc.): Parent reported duration and severity. Change in one of two characteristics for +/-1 score, +/-2 score for change in two of the characteristics.
  - Non-communicating Children's Pain Checklist-Revised (NCCPC-R): MCID = 0.25 SD

The MDRI will be calculated as the sum of scores from the components. Subjects will receive a score for each component of the MDRI listed above. A score of 0 will be given for a change in score less than the MCID. A score of +1 (improvement) or -1 (worsening) will be given for a change in score of  $\geq 1$  MCID and  $< 2$  times MCID. A score of +2 (improvement) or -2 (worsening) will be given for a change in score of  $\geq 2$  and  $< 3$  times MCID. A score of +3 (improvement) or -3 (worsening) will be given for a change in score of  $\geq 3$  times MCID. Seizures and movement disorder outcomes will be scored as described above.

3. Individual Clinical Response (ICR) – 5 most impactful clinical problems reported by the caregiver. Sum using 5-point Likert scale for each ICR element.

4. Gait: Qualitative assessment by physical therapist (i.e. improved, no change, worsened).
5. Stair climb/descent: Time and quality of movement.
6. Sleep Diary (1-week recall): Sum of the number of overnight awakenings, average duration of overnight awakenings, and duration of time for initial sleep onset at bedtime.
7. Stooling Survey.

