f After written informed consent but before study treatment initiation, only SAEs associated with protocol-imposed interventions will be recorded. After study drug initiation, all AEs, SAEs, and pregnancy will be recorded until week 44 or the Early Termination visit. If a subject is discontinued from the study prematurely, AEs and SAEs will be recorded at the Early Termination visit.

g During these contacts, study staff will ask about dose administration and seek information on AEs and SAEs by specific questioning. Information on all AEs and SAEs should be recorded in the subject's medical record and on the AE eCRF.

h Diaries will be completed at week -6 to avoid the potential impact of travel on these outcomes.

i Plasma and serum samples collected and stored for PK and anti-drug antibody studies.

j Buffy coat will only be collected on Week -8, Day 1, and Week +36.

k Week +24 safety labs only if dose was increased at week +16.

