### **27.7 Dosing**

In this study anakinra subcutaneous (SC) will be administered at a dose level of 100 mg SC once daily. Anakinra will be administered every other day in patients who have severe renal insufficiency or end stage renal disease (defined as creatinine clearance < 30 mL/min as estimated from serum creatinine levels).

**Dose will be increased to 200 mg SC once daily**, with a maximum dose limit of 8 mg/kg/day, at **Week +8** if the change in at least one of the two most bothersome outcomes selected by the parents/guardians at the Day 1 visit has not improved by  $\geq$  the MCID as defined in Section 9.1. If the MCID is not achieved after 8 weeks on maximum trial dose of 200mg (max dose 8 mg/kg/day), **treatment with anakinra may be discontinued after a review and discussion between the study PI and subject's parent(s) of their child's individual results from all study outcome measures.**

**Dose will be increased to 200 mg SC once daily**, with a maximum dose limit of 8 mg/kg/day, at **Week +16** if the change in at least one of the two most bothersome outcomes selected by the parents/guardians at the Day +1 visit have worsened by  $\geq$  the MCID as defined in Section 9.1 between week +8 and week +16, after an improvement from Day +1 to week +8. If the MCID is not achieved after 8 weeks on maximum trial dose of 200mg (max dose 8 mg/kg/day), **treatment with anakinra may be discontinued after a review and discussion between the study PI and subject's parent(s) of their child's individual results from all study outcome measures.**

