**For example:**

- At week +8, if a subject has not improved in the chosen items then the dose will be increased to 200 mg SC daily.
- At week +8, if a subject has improved, then the dose stays at 100 mg SC daily. However, if this individual then has worsening of the two most bothersome outcomes from week +8 to week +16, after improving from day 1 to week +8, the dose will be increased to 200 mg SC daily at that point (i.e. increase at week +16 after not increasing at week +8).

**Dose will be decreased by 50 mg SC once daily** at any time throughout the study if a participant develops any of the following:

- Neutropenia  $<1200$  cells/microliter persistent for  $\geq 2$  weeks
- Thrombocytopenia  $<50 \times 10^9$  platelets/liter persistent for  $\geq 2$  weeks
- Mild/moderate hypersensitivity reactions including urticaria, rash, and pruritis
- Participants develops a CTCAE grade 3 AE

**Anakinra will be stopped** if the AE above does not resolve within 2 weeks of decreasing the dose by 50 mg SC once daily. Anakinra will be restarted at 0.5 times the last dose administered once the AE is resolved. If the AE recurs with restarting anakinra, it will be discontinued and the subject monitored per protocol.

The starting dose is the same dose level as recommended for adult rheumatoid arthritis patients. The dose escalation is within the range of the recommended dose in Neonatal onset multisystem inflammatory disease (NOMID), including also pediatric patients, is related to body-weight, with a recommended starting dose of 1-2 mg/kg up to a maximum dose of 8 mg/kg.

Smaller children with lower body weight need higher dose levels/kg body-weight in order to achieve similar anakinra serum exposure as in older, heavier children, due to a higher capacity to eliminate anakinra/kg body-weight, based on pharmacokinetic data in 22

systemic-onset juvenile idiopathic arthritis (SJIA) pediatric patients in the age range 2-17 years.

As an example, based on this study, a patient with a body-weight of 20 kg is predicted to require a dose of 4 mg/kg/day to achieve similar anakinra exposure (area under the curve [AUC]0-24h, ss and Cmin, ss) as a dose of 100 mg in a 50 kg patient. Additional examples are given below:

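### The secondary 8-week treatment window follows the dose, and the dose follows the response, so on the literal reading the MDRI contrast leans towards anakinra even if the drug does nothing

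*Protocol*

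**What the plan says.** Protocol Section 9.1 opens the secondary endpoints with "Within individual change over 8-week treatment period (on maximum effective and tolerated dose) compared to change over 8-week observational period". The same sentence adds a second contrast with fixed ends, "and from Day 0 to Week +36 (i.e. treatment phase) in" the listed outcomes. The first contrast has a length and a dose condition but no calendar weeks and no stated baseline.

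The only upward dose rule is in Section 27.7. Its Week +8 trigger for a higher dose is that "the change in at least one of the two most bothersome outcomes selected by the parents/guardians at the Day 1 visit has not improved", judged against the MCID. The worked example says that "if a subject has not improved in the chosen items then the dose will be increased to 200 mg SC daily", and that "if a subject has improved, then the dose stays at 100 mg SC daily". A later escalation at Week +16 follows a worsening "between week +8 and week +16, after an improvement from Day +1 to week +8". Section 9.1 takes the symptoms that drive this rule from the MDRI measures, and the MDRI is itself on the secondary list.

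In the Section 10.2 schedule, caregiver instruments are completed at Week -8 (diaries at Week -6), Day 1 and Weeks +8, +16, +36 and +44. Gait and stair climb are not done at Week +8 or +16. Week +24 carries laboratory tests alone: "Week +24 safety labs only if dose was increased at week +16".

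The analysis text in Section 12.2 works with fixed periods: pre-observation, 8 weeks of treatment, 36 weeks of treatment and post-observation. Week +16 is not among them.

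**The concern.** If the window is the eight weeks on the final dose, the outcome decides which window is analysed. A subject who improved by chance at Week +8 keeps the window in which that happened. A subject who did not improve gets a fresh window, which tends to start from a chance-poor Week +8 score and so drifts upward on re-measurement. The observational period, Week -8 to Day 1, gets no second draw. The study is open label with no concurrent control, so nothing offsets the asymmetry.

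At stake is whether an 8-week MDRI gain can be read as a drug effect. A subject escalated at Week +16 would need an efficacy score at Week +24, which is not scheduled, so that subject's window cannot be computed at all.

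**Working it through.** **The plan's own figure.** The protocol gives no operating characteristic for this contrast. Its one relevant figure is the Section 12.3 margin of about half a standard deviation for a paired difference at n = 20. It reproduces: t(0.975, 19)/√20 = 2.093/4.472 = 0.468 SD. It is not in dispute.

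**Inputs from the protocol.** n = 20; MCID m = 0.25 SD (SBRS, APSI, NCCPC-R); two-sided 5% level; signed-rank test for the MDRI; MDRI components scored from -3 to +3 in MCID steps.

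**Assumptions not in the protocol.** Test-retest reliability r; visit noise independent between visits; no drug effect; two chosen symptoms, independent of each other in step 1. Both readings of the Week +8 rule are carried: escalate if either symptom fails, or only if both fail.

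**Step 1: bias on one chosen symptom, in closed form.** Let d be the Day 1 to Week +8 change. Its SD is σ = √(2(1-r)). Put z = m/σ, p = P(d ≥ m) = 1 - Φ(z), and A = E[d; not escalated], the part of the mean contributed by non-escalated subjects.

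- Either fails: A = σφ(z)·p.
- Both fail: A = σφ(z)·(1-p).

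Half of any Day 1 to Week +8 change is expected to be Week +8 noise. The Week +8 to +16 change among escalated subjects therefore contributes -½E[d; escalated], which equals +½A because E[d] = 0. Hence:

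- literal window: bias = A + ½A = 1.5A;
- escalated subjects measured from Day 1: bias = A - ½A = 0.5A;
- fixed Day 1 to Week +8 for everyone: bias = 0.

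At r = 0.8: σ = 0.632, z = 0.395, φ(z) = 0.369, σφ(z) = 0.233, p = 0.346.

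- Either fails: 1.5 × 0.233 × 0.346 = 0.12 SD. Share escalated: 1 - 0.346² = 88%.
- Both fail: 1.5 × 0.233 × 0.654 = 0.23 SD. Share escalated: 0.654² = 43%.
- From Day 1: 0.04 and 0.08 SD.

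For r = 0.7, 0.8 and 0.9 the literal bias is 0.16, 0.12 and 0.07 SD (either) and 0.28, 0.23 and 0.16 SD (both). Simulated trials give the same values.

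**Step 2: the MDRI, the outcome actually on the secondary list.** Null trials with a six-component MDRI and the signed-rank test of window change minus observational change, at r = 0.75, ignoring Week +16 escalation:

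| Caregiver error correlation | Rule | Null MDRI mean, literal | Rejects, literal | Rejects, escalated from Day 1 | Rejects, fixed Week +8 |
|---|---|---|---|---|---|
| 0 | either | +0.8 | 6.4% | 5.3% | 5.7% |
| 0 | both | +1.4 | 12.3% | 5.9% | 4.9% |
| 0.3 | either | +2.1 | 11.2% | 5.3% | 4.8% |
| 0.3 | both | +3.2 | 22.0% | 6.8% | 4.9% |

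With 4,000 trials per cell the simulation error is about 0.4 percentage points: √(0.064 × 0.936/4,000) = 0.0039. The first row is therefore barely distinguishable from its fixed-window value in test size, although its mean is clearly shifted. Further runs over r = 0.7 to 0.9 gave 7% to 8% (either) and 13% to 14% (both) with independent instruments, and about 8% to 24% at correlation 0.3. Taking the runs together, the independent-instrument figures are 6% to 8% and 12% to 14%.

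**Step 3: how far it reaches.** With independent errors, components that do not drive the rule show no bias. At correlation 0.3 they pick up some. If visit noise is a random walk instead, the literal window still favours the drug on a chosen symptom (+0.17 to +0.54 MCID for either, +0.43 to +0.84 for both), while the Day 1 version of the Week +8 rule is close to zero.

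**The case against.** The strongest reply is that Section 9.1 states neither weeks nor baseline, so the Week +8 to +16 window is inferred. Section 12.2 lists only fixed 8- and 36-week periods, which suggests that the analyst may never use it. If escalated subjects are measured from Day 1, MDRI test size is about 5% to 7%. This stands as a limit on size. It does not clear the text: Sections 9.1 and 12.2 then disagree, and the dose parenthesis has no function unless it selects a window.

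The contrast is also secondary, in a pilot sized by feasibility, and Section 12.2 already promises caution over unadjusted secondary results. That lowers the severity. Caution about multiplicity does not, however, address a directional bias.

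A reader might infer more than the documents support:

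- *A false-positive rate of 11% to 31%.* At r = 0.8 that is the rate for the average of the two chosen symptoms. They belong to the Phase 2 primary endpoint, which carries no dose condition, and are not on the secondary list.
- *Every secondary comparison is affected.* The Week +36 contrast has fixed ends, and gait and stair climb have no Week +8 or +16 assessment, so neither window can be computed for them.
- *The bias always favours the drug.* It does on the literal reading for outcomes that drive the rule or share rating error with it. It does not for outcomes with independent error, and on the Day 1 reading with random-walk noise it is about zero or slightly negative.
- *The bias cannot be undone.* The scheduled visits already allow fixed windows.

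**Conclusion.** The concern holds for the literal reading of the secondary 8-week contrast. The window is selected by response, and under no drug effect the MDRI, and plausibly other caregiver-rated outcomes sharing its rating error, shifts towards benefit. The inflation of the 5% test is modest on the either-fails reading with independent instruments and material if both must fail or if caregiver errors correlate. These sizes rest on assumed reliability, noise structure and rater correlation, so the direction is firmer than any single figure. Two defects need no such assumptions: the Week +16 escalators' window cannot be computed, and Section 9.1 does not match Section 12.2. The point merits a should-fix. It does not undermine the Phase 2 primary or the Week +36 contrast.

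**What to change.** In Section 9.1, delete the parenthesis on dose from the secondary endpoint sentence. For outcomes assessed at Week +8, state that Day 1 to Week +8 is compared with Week -8 to Day 1 for every subject regardless of dose. Keep Day 1 (written there as Day 0) to Week +36. Make the time points in Section 12.2 agree, and report change on the escalated dose in a separate descriptive table.

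The rule and the worked example in Section 27.7 describe the escalation trigger differently (at least one outcome, against the chosen items or both outcomes). They must be reconciled, because the wording decides who is escalated. No view is taken here on which is right.

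The cost is a phrase and matching analysis wording. No visit, data item or dosing rule changes because of the window itself. The one loss is that the 8-week contrast then describes the starting dose only, with the higher dose reflected at Week +36 and in the descriptive table.

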### ***10.6 Sleep***

Sleep will be assessed using two methods:

1. Sleep Diary – Parents will record daily for 1 week during Week -6 (to avoid the effects of travel on sleep) and then 1 week prior to each study visit after that, the following information:
  - Number of night time awakenings
  - Duration of nighttime awakenings

- Number of consecutive hours of sleep overnight
- Length of time to get child to sleep at bedtime (first of the night)
- Number of daytime naps
- Length of daytime naps

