### **10.14 Individual Clinical Response (ICR)**

The 5 most important clinical problems will be determined by the caregiver. Examples will be offered based on previous work that include sleep disturbances, hyperactivity, frustration/impulse control/aggressive behaviors, feeding, anxiety, unhappiness, communication, social deficits, digestive issues and toileting, pain, illness/vulnerability to illness, fatigue, seizure, mobility, and gait. The caregiver will rate their top 5 outcomes on a 5-point Likert scale as follows:

0 - Not stressful

1 - Sometimes creates stress

- 2 - Often creates stress
- 3 - Very stressful on a daily basis
- 4 - So stressful sometimes we feel we can not cope

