### **Secondary objective**

Outcome variables include Individual Clinical Response (ICR, 0~25: sum of the top 5 domains on a 5-point Likert scale), Gait analysis results (improved, no change, worsened), Stair climb/descent (time and quality of improvement), Sleep diary (sum of the number of overnight awakenings, average duration of overnight awakenings, and duration of time for initial sleep onset at bedtime), and Stooling survey results. For univariate analyses, similar statistical tests will be used as ones used for the primary objective, depending on the data type of the outcome for comparing two study periods. For multivariate analyses, mixed effect models (linear for continuous outcomes and non-linear such as multinomial logistic regression for categorical outcomes and Poisson (or Negative Binomial regression model, if over-dispersion is apparent) for count outcomes) will be used using 2-4 different time points (pre-observation, 8, 36 week treatment, post-observation periods) as within subject factor. Covariates such as sex and age will be considered in multivariate models if they are found to be statistically significant in changes of outcomes. Sub-scale analyses will be conducted if changes in the composite score are found to be statistically significant or are reached to a clinically meaningful boundary. We expect to have full data without any missing for all outcomes. However, in case of missing data, two imputation methods, i) last observation forward, ii) multiple imputation assuming missing at random, will be considered.

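### The sleep-diary endpoint adds a count to an average duration and an onset time, so it can worsen while total time awake falls; separately, the ICR range should be 0–20, not 0–25

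*Protocol*

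**What the plan says.** **Sleep diary.** Section 9.1, secondary endpoint 6, is the one-week sleep diary, scored as "Sum of the number of overnight awakenings, average duration of overnight awakenings, and duration of time for initial sleep onset at bedtime". The secondary-objective text of section 12.2 uses the same construction: "Sleep diary (sum of the number of overnight awakenings, average duration of overnight awakenings, and duration of time for initial sleep onset at bedtime". Section 10.6 lists what parents record each day for a week. The relevant entries are "Number of night time awakenings", "Duration of nighttime awakenings" and "Length of time to get child to sleep at bedtime (first of the night". None of these places gives a time unit, a weight or a standardisation. They also do not say whether the count is per night or per week, or whether the recorded duration is per awakening or the night's total.

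**ICR.** Section 9.1, secondary endpoint 3, gives "Sum using 5-point Likert scale for each ICR element". Section 10.14 has the caregiver rate five problems, with item codes that start at 0 and end at "4 - So stressful sometimes we feel we can not cope". Section 12.2 describes the outcome as "Individual Clinical Response (ICR, 0~25: sum of the top 5 domains on a 5-point Likert scale".

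**The concern.** A count and two durations have no common scale. If durations are in minutes, one awakening weighs the same as one minute; if they are in hours, it weighs the same as one hour. The sign of a child's change can then depend on the unit.

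Fixing the unit removes only part of the problem. The mean length of the remaining awakenings rises whenever the short ones disappear, so a child who wakes less often and for less total time can still score worse. That fault comes from the endpoint definition itself, not from a detail left to a later document.

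Better sleep is one of the effects hypothesised in section 4.0, and fewer awakenings is a plausible form of it. Section 12.2 plans paired tests and mixed models for outcomes of this kind in 20 subjects, so a few changes with the wrong sign would matter.

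The ICR point is a plain mismatch between two sections. It affects how the scale is described.

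**Working it through.** **ICR: the plan's own figure first.** The total runs from 5 × (item minimum) to 5 × (item maximum).

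- Section 10.14 coding, 0 to 4: 5 × 0 = 0 to 5 × 4 = 20.
- Coding 1 to 5: 5 to 25.
- Coding 0 to 5: 0 to 25, but that is a six-level item.

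The stated 0–25 therefore does not follow from any five-point item. The protocol's own coding gives 0–20, and the stated upper limit is 25/20 = 1.25 times the attainable maximum.

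**Sleep diary.** The protocol gives no diary values, so all inputs below are assumed. Let *n* be the number of awakenings, *d* their average duration in minutes, *o* the sleep-onset time in minutes, and *u* = 1 for minutes or 60 for hours. Then

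S = n + d/u + o/u, and the change is ΔS = Δn + (Δd + Δo)/u.

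Example 1: in one week there are seven awakenings of 10 min and seven of 60 min, and onset takes 30 min. The seven short awakenings then disappear and onset is unchanged.

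- Average before: (7 × 10 + 7 × 60)/14 = 490/14 = 35 min. Average after: 60 min.
- Overnight time awake: 490 min per week before, 7 × 60 = 420 after.

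| Scoring | Before | After | Direction |
|---|---|---|---|
| Weekly count, minutes | 14 + 35 + 30 = 79 | 7 + 60 + 30 = 97 | worse |
| Weekly count, hours | 14 + 0.583 + 0.5 = 15.08 | 7 + 1 + 0.5 = 8.5 | better |
| Nightly count, minutes | 2 + 35 + 30 = 67 | 1 + 60 + 30 = 91 | worse |
| Nightly count, hours | 2 + 0.583 + 0.5 = 3.08 | 1 + 1 + 0.5 = 2.50 | better |

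The result does not depend on whether the count is weekly or nightly. Onset is unchanged and cancels from the difference, so its scaling does not matter either.

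Example 2, the opposite error: a night with 3 awakenings averaging 20 min and 30 min onset becomes one with 4 awakenings averaging 20 min and 20 min onset. Overnight time awake rises from 60 to 80 min; with onset included it rises from 90 to 100 min. In minutes the sum falls from 53 to 44 (better). In hours it rises from 3.83 to 4.67 (worse).

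**When there is no reversal.**

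- All components improve or hold: 4 awakenings/20 min/40 min onset to 3/20/20 gives 64 to 43 in minutes and 5.00 to 3.67 in hours. The units agree.
- Awakenings of similar length: in a week with seven of 10 min and seven of 12 min, losing the shorter ones gives 14 + 11 + 30 = 55 to 7 + 12 + 30 = 49 in minutes. The score improves, as it should.

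In minutes, with onset unchanged, the score rises only if the average lengthens by more minutes than the count drops. In Example 1 that is 25 against 7, hence +18.

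**The case against.** The strongest reply is that no composite was intended. The diary is daily, so the phrase could list three weekly summaries: a summed count, an averaged duration and an onset time. Section 12.2 also provides Poisson or negative binomial models for count outcomes, and the number of awakenings is an obvious candidate. On that reading the problem of mixed units disappears. The reading is possible but less natural, because in both sections one sum governs the whole list for one endpoint. Either way the sentence needs rewriting.

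A second reply is that the time unit may be fixed on the diary form or in a statistical analysis plan, neither of which is at hand. That is fair, and the missing unit alone would be a weak point. It does not answer the use of an average, which can reverse the sign with minutes fixed.

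The third reply concerns consequence, and it stands. This is the sixth of seven secondary endpoints in a pilot sized by feasibility, and section 12.2 already asks for caution with unadjusted secondary results. The CSHQ is the sleep measure in the MDRI, and its subscales include night wakings, sleep onset delay and sleep duration (section 10.6). The diary score is not among the measures listed for dose escalation.

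A reader might also infer that the database will accept impossible ICR totals up to 25. Section 12.5 says only that entries outside expected ranges will be flagged. It gives no ICR limit and does not say that totals are entered, so this is something to check, not a finding.

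**Conclusion.** The point holds in limited form. As naturally read, the sleep-diary score can report worse sleep when a child wakes less often and for less total time, and it can give opposite directions in minutes and in hours. Example 1 shows both: +18 in minutes and −6.58 in hours, while overnight time awake falls by 70 min per week.

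This rests on the composite reading and on assumed diary values. The values establish that a reversal can occur; the protocol holds no data from which to say how often. A reader might infer that losing short awakenings always raises the score, or that the trial's conclusion about sleep will be wrong. The documents support neither: several patterns give the right sign in both units, and the CSHQ is a separate sleep measure.

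The endpoint definition should be revised, although it is secondary. The ICR range is a certain but minor labelling error, which changes no item score, total or test.

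**What to change.** - **Sleep diary (sections 9.1 and 12.2).** Replace the sum with mean minutes awake per night: sleep-onset minutes plus total minutes of overnight awakenings (number × average duration), computed within each night and averaged over the diary week. Report the number of awakenings separately. In Example 1 this gives 490/7 + 30 = 100 falling to 420/7 + 30 = 90, the right direction. If three separate summaries were meant, name them and drop the sum.
- **Diary form.** Confirm the time unit and whether duration is recorded per awakening or as the night's total. All the items are already collected (section 10.6), so no new data are needed.
- **ICR (section 12.2).** Change the range to 0–20 to match section 10.14, and check that any database limit agrees.

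The cost is a few lines of wording plus a small credibility cost. The study is open-label, and the version 1.7 entry in the version history already draws on experience with the enrolled cohort, so this would redefine an endpoint after data collection began. Record it with its reason, as the closing paragraph of section 12.2 requires for deviations, and report the present sum, in stated units, as a sensitivity analysis.
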